### Entomological evaluations

The primary entomological endpoint (EIR) will be measured using CDC miniature light traps in eight randomly selected households with open eaves in 24 core cluster areas (12 clusters per study arm), every month (Table 1) [43]. Eligible households will contain children enrolled in the cohort study. In each household a CDC miniature light trap will be positioned 50 cm away from a single sleeper protected by a LLIN. To compare the extent of outdoor biting and transmission, every other month Furvela tent trapping will be undertaken in coordination with indoor light trapping [44]. One tent will be used in each cluster per night, set close to one of CDC light trapping households. Indoor and outdoor mosquito collections will be identified to species complex by microscopy [45] and the numbers of *An. gambiae* s. l., *An. funestus* s. l. and other *Anopheles* recorded. In each trap collection, a subset of *An. gambiae* s. l*.* and *An. funestus* s. l. will be speciated by PCR [46, 47]. In the case of *An. gambiae* s. l. knockdown resistance status (presence of *kdr* L1014S or L1014F alleles; previously *kdr-*east or *kdr*-west) will be determined by PCR [48]. *Plasmodium falciparum* sporozoite infection rates in *An. gambiae* s. s*., An. arabiensis* and *An funestus* s. l. will be assayed using a circumsporozoite protein (CSP) enzyme-linked immunosorbent assay (ELISA) [49].

To compare indoor mosquito resting density between the two study arms, early morning pyrethrum spray catches (PSCs) will be conducted in one household per cluster (total of 48 households). PSCs will be performed before intervention (during the long rainy season in May/June 2015), once during the cool dry season (August/September 2015) and during the second long rainy season (May/June 2016) (Table 1). To determine host feeding preferences, all blood fed malaria vectors will be squashed and dried onto filter papers and blood meal sources identified by ELISA [50].

Insecticide resistance profiles in both study arms will be compared before (during the long rainy season in May/June 2015) and after intervention (during the second long rainy season in May/June 2016) using three different bioassays: WHO cylinder bioassays for resistance to pyrethroids [51], CDC bottle bioassays for resistance to the two non-pyrethroid ITWL active ingredients [52] and resistance to pyrethroids. All assays will be performed using locally collected field populations of *An. gambiae* s. l. and *An. funestus* s. l. Larvae will be collected by sampling multiple breeding sites from at least six clusters per study arm, and reared to adults in the NIMR insectary; all bioassays will be performed using 2–5 day old unfed adult females.

Resistance to alphacypermethrin and permethrin will be measured using WHO cylinders at standard diagnostic dosages [53]. In lieu of WHO cylinder bioassays, CDC bottle bioassays will be used to determine the 50 and 99 % lethal doses (LD_50_ and LD_99_) to the two non-pyrethroid ITWL active ingredients. To measure intensity of pyrethroid resistance, the susceptible reference strain *An. gambiae* s. s. Kisumu will be exposed to a range of alphacypermethrin and permethrin dosages (0.001 μg/ml–0.5 μg/ml) to determine the LD_50_ [54]. A range of dosages will then be chosen to test against wild collected adult *An. gambiae* s. l. and *An. funestus* s. l (and F1 generations) that kill between 10 and 100 % before calculating the LD_50_ and comparing the resistance ratios to the reference strain. The intensity of resistance tests will be repeated on field collected specimens at the end of each transmission season. For all WHO resistance tests, six replicates of 20 mosquitoes and one control replicate will be assayed and percent knockdown will be observed every 15 min during 1 h of exposure; mortality will be recorded after 24 h. Surviving and dead mosquitoes will be analyzed for species identification and *kdr* resistance status, as described above.

### Intervention monitoring: ITWL

Prior to ITWL installation, quality control of the ITWL material will be assessed using WHO cone [55] and modified WHO cylinder bioassays [51] from a random sample of four rolls from each of five production lots (20 rolls total). From each ITWL roll, three 25 × 25 cm squares will be cut from a 2.5 × 1 m section for testing. Four WHO cone assays will be tested per ITWL sample for a total of 12 cone assays per roll. WHO cones will be fixed to the ITWL sample with frames and ten 2–5 day old unfed susceptible *An. gambiae* s. s. Kisumu mosquitoes or wild collected adult *An. gambiae* s. l will be exposed for 30 min; knockdown will be recorded after 1 h and mortality after 24, 48 and 72 h; the same experimental conditions will be used for WHO cylinder bioassays.

ITWL durability surveys will be conducted in 5 randomly selected households from eight intervention clusters (total of 40 households) at three, six and 12 months after intervention. At each follow-up, interviewers will survey the house to evaluate the condition of the ITWL installation and to record failed fixings, material tearing, causes of damage, proportion of walls still covered with ITWL and any evidence of ITWL repair, maintenance or attrition. In the same houses, ITWL in situ bioefficacy will be assessed using five WHO cone bioassays conducted as described above, at two wall heights (<1 m and >1 m from the floor) for a total of 10 bioassays per house. In addition, 5 × 5 cm samples of ITWL will be cut from house walls and insecticide content measured using HPLC according to the Collaborative International Pesticides Analytical Council (CIPAC) protocol.

### Intervention monitoring: LLINs

As part of the standardized questionnaire administered during each monthly cohort follow-up, LLIN coverage, use and attrition will be monitored. Participants will be asked about number of LLINs owned and number of sleeping places covered at the household level using a modified version of the WHO LLIN durability questionnaire [56].

### Social acceptability and economic evaluations

To identify social, cultural and other factors that may affect acceptability and uptake of ITWL and LLINs in the study area, a series of FGDs and IDIs will be undertaken. Four FGDs will be conducted in two randomly selected villages from each study arm prior to intervention and in the same villages after ITWL installation and LLIN distribution (total of 16 FGDs). FGDs will be conducted with small groups (8–12 participants) of men and women separately to reflect the different roles played in Tanzanian society and to ensure that all members will feel able to contribute to the discussion. In each village, one FGD will comprise heads of households and the other mothers of children <5 and mothers of children aged 5 to 11 years old. FGDs will be led by a trained moderator who will use a guide with open-ended questions to explore with the group a series of broad topics relating to malaria, disease prevention, ITWL concept and installation, LLIN use and healthcare seeking behavior and access. FGDs will be digitally recorded with consent from participants and a note-taker will document all non-verbal communications.

IDIs will be conducted with village or hamlet leaders, CHWs from village health facilities and ITWL installers to explore the opinions of key individuals who may play important roles in influencing community members’ perceptions of ITWL and LLIN use. Four IDIs will be conducted per study arm prior to intervention and with the same individuals after ITWL installation and LLIN distribution (total of 16 IDIs). The IDIs will cover a range of similar topics to the FGDs. IDIs will be conducted by a trained interviewer and digitally recorded with participant’s consent; non-verbal communication will be documented by hand. Informal community observations relating to major study activities, including community sensitization meetings, ITWL installation and LLIN distribution, will also be recorded by the study teams. Following the FGDs and IDIs, the main themes identified will be used to design a standardized, closed-ended quantitative acceptability questionnaire to be administered at three, six and 12 months post-intervention.

To assess the cost-effectiveness of ITWL + LLINs vs. LLINs alone, supplementary data will be collected from an additional ‘older’ sub-set of participants (≥12 years old) who occupy the same households as members of the main study cohort. From the baseline census, it is estimated that the 110 children/core area will represent 70 households and each core household will contain an average of three ‘older’ individuals. To determine the incremental effectiveness of ITWL across the entire age spectrum, during monthly cohort follow-ups, the key informant will report whether within the preceding 30 days, any ‘older’ household member(s) experienced a febrile illness and what, if any, treatment was received; if the informant themselves report a febrile illness, they will be asked to be tested with an mRDT immediately.

To estimate the economic cost per malaria episode, macro-cost analysis of hospital statistics from Teule Hospital and Mkuzi Health Centre (Muheza’s only district hospital and major health centre, respectively) will be used to determine the medical costs (cost per bed day and per outpatient visit) associated with an episode of clinical malaria and a household economic survey will measure additional out-of-pocket expenditures associated with care-seeking, non-medical direct and indirect costs and the impact of malaria on household food security. The economic questionnaire will be conducted on a monthly basis among all hospitalized cases, identified during the cohort visits, and an additional, randomly selected 14 % of households containing cohort children, to detect malaria cases treated in other settings (e.g. ambulatory, treated at home or with no treatment). During the economic questionnaire, all household members who report a febrile illness during the preceding 30 days will be interviewed and if they were not tested for malaria, they will be asked to take an mRDT; for children under 18 years old, the mother will be interviewed on their behalf. Any reduction in malaria-related school absenteeism by cluster will be measured during the monthly cohort visits, relative to the number of days two local schools was operational (verified by trusted community leaders and/or head teachers).

To measure the cost of LLINs distribution and ITWL installation, a micro-costing or ingredient approach to determine the personnel effort and materials, and a top-down costing approach to estimate the indirect cost associated management, oversight, transportation, and monitoring will be used. Additional meta-data on the cost of IRS implementation in other Tanzanian districts will be provided by Research Triangle Institute (RTI) and recently published estimates of the effectiveness of IRS in combination with LLINs [5], will be compared with the cost-effectiveness of ITWL.

### Trial oversight, safety considerations and handling withdrawals/drop-outs

Trial oversight will be provided by a Data and Safety Monitoring Board (DSMB) comprising three independent clinical and epidemiological experts. The role of the DSMB is to safeguard the interests of study participants as well as assess the safety and effectiveness of the study interventions. Independent data reviews by the DSMB will be conducted every 3 months throughout the study year.

Any adverse events (AEs) arising from either LLINs or ITWL will be closely monitored and documented. Interceptor® LLINs have been fully evaluated by the WHO Pesticide Evaluation Scheme (WHOPES) and approved for vector control; the product will be used in compliance with their recommended guidelines [57]. The non-pyrethroid insecticides in the ITWL have low mammalian toxicity and good safety profiles [58]. The proprietary combination formula used in the ITWLs has passed an initial environmental examination (IEE) conducted by an independent regulatory agency; hazard quotients for continuous habitation in a residence with ITWL were far below the acceptable threshold. All ITWL installers, who will receive the highest levels of exposure, will wear personal protective equipment (PPE; a minimum of gloves, long sleeves and eye protection) during intervention implementation. ITWL installers will undergo pre-installation, mid-way and post-installation medical examinations, which will include monitoring for any AEs.

During the ITWL intervention period, all core and buffer households will be visited 6–10 days following installation to document any AEs. Adverse event monitoring will also occur among ITWL installers through a passive AE monitoring chain. Throughout the study year, AEs will be monitored actively in each monthly cohort follow-up visit, during which the clinical team will ask the parents of cohort participants to report all AEs for any members of their household. Cohort members will also be given a study card to take to local health facilities, which will be used to record any AEs arising between monthly study visits. Other study participants will report AEs at any point to the CHWs, health facility or study team through a passive AE monitoring chain in both core and buffer areas. All AEs such as skin or eye irritation, respiratory problems, dizziness, nausea etc., will be graded in terms of severity (mild, moderate or severe), seriousness (based on patient outcome) and relatedness to the intervention by comparison with the control arm [58]. Appropriate management for any AE will be provided according to local guidelines and the outcome of AEs, including resolution, persistent disability, birth defect or death will be recorded.

In the case of a serious adverse event (SAE), the study clinician will record and manage the SAE in accordance with Good Clinical Practice (GCP) and report these to the PI who will inform the responsible member of the trial DSMB. Excessive grouping of SAEs by village or cluster will be reported to the DSMB and respective institutional ethics committees. A determination by the DSMB that there is potential harm to participants or the environment caused by the interventions will result in discontinuation of the study.

If an individual or household wants to terminate their participation, no further follow-up will be performed. If a cohort participant misses three consecutive monthly follow-up visits, they will be excluded from the study analysis. There will be no participant replacement during the surveillance period. If a household withdraws that was participating in the durability monitoring, it will be substituted with a neighbouring house of similar construction, where possible; there will be no other household or village replacements.

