### Design

A parallel cluster randomized controlled study design will be used as ITWL is a community-level intervention and a village cluster is a suitable unit for randomization. The study monitoring period will be 12 months, beginning December 2015, which will encompass one long (February-May, 2016) and one short rainy season (October–December, 2016) and two intervening dry seasons (Table 1). Following household enumeration, baseline socio-demographic, economic and household construction data will be collected. At study onset, all participating households will be provided with UC of LLINs, defined as one LLIN per every two persons. Clusters will then be randomized into two equal groups; all households in villages from one group will receive ITWL installed on interior house walls.

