### Randomization and blinding

In cluster randomized controlled trials it is particularly important to minimize imbalance for factors known to be highly correlated with disease outcome, in this case house construction/presence of open eaves and LLIN usage. Since all households will be provided with LLINs and the majority of homes have open eaves (89 % during baseline surveys), clusters will be stratified into two groups based solely on malaria prevalence; clusters in each stratum will then be randomly assigned to the two study arms. Stratified randomization of villages will reduce the likelihood of chance imbalances between study arms but as only a relatively small number of units can be randomized in such a cluster design, both groups cannot be assumed comparable for all factors. Baseline data on malaria prevalence and haemoglobin concentration collected from all enrolled cohort participants will be used to assess disparity in disease burden at the village level prior to study monitoring.

Observer bias will be reduced where feasible; because of the visible and obvious nature of the intervention, it is not possible to conduct ITWL installation in a blinded manner. Mosquito collector bias will be reduced by using standard CDC miniature light traps and Furvela tent traps, which do not rely on the technical ability of the fieldworker to collect specimens. Trap catches will be examined by a different person to the trap collector and they will be blinded to the trap location and intervention status. The intervention implementation, for both ITWL installation and LLIN distribution, will be monitored closely for quality and to document any bias between the clusters. Epidemiological data entry will be conducted using smartphones to minimize errors in collection; GPS location and time of questionnaire administration will also be recorded to ensure that interviews are appropriately conducted and adequate time has been devoted to data collection.

Loss to follow-up will be minimized through the use of community health workers (CHWs) from each cluster to ensure children are available during monthly study visits. In the event of missing participants, the study team, assisted by CHWs, will undertake home visits to locate cohort members or may extend the monthly visits to each cluster to sample participants who are temporarily unavailable. Extended periods of time spent living away from a participant’s cluster will be recorded and factored into the analysis.

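### Adverse events are to be judged related by comparison with the control arm, but the post-installation household visit, as written, finds events in the ITWL arm only

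*Protocol article*

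**What the plan says.** The Protocol article, under Trial oversight, safety considerations and handling withdrawals/drop-outs, describes several ways of finding adverse events.

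- **A timed household visit.** In the ITWL intervention period, "all core and buffer households will be visited 6–10 days following installation to document any AEs", one visit per household.
- **Monthly cohort visits.** "AEs will be monitored actively in each monthly cohort follow-up visit", with parents asked about everyone in the household. Cohort children also carry a card on which health facilities record events between visits.
- **Passive reporting.** Other participants report "through a passive AE monitoring chain in both core and buffer areas".
- **Installers.** They have medical examinations before, midway through and after installation, plus their own passive chain.

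The section then applies one grading rule to all adverse events. Besides severity and seriousness, each is graded for "relatedness to the intervention by comparison with the control arm".

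The Design section gives installation to half the clusters: "all households in villages from one group will receive ITWL installed on interior house walls". The Randomization and blinding section states that "it is not possible to conduct ITWL installation in a blinded manner".

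**The concern.** A control arm is a sound reference for relatedness only if events are looked for in the same way in both arms. Here the control arm is the reference for all events, yet one active source has no stated control counterpart. The examples of adverse events in the article are common, non-specific complaints of the skin, eyes, breathing and so on. Such complaints occur without any exposure and are reported more often when someone calls and asks. With equal true risk in both arms, the extra visit alone would produce an excess in the ITWL arm, and the stated rule would read that excess as relatedness.

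The error could also run the other way. A reader who notices the one-sided visit may discount a real early reaction to the lining as an artefact. In either case the comparison shown to the Data and Safety Monitoring Board (DSMB) would be harder to interpret than it needs to be.

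**Working it through.** The plan states no figure for this point, so there is none to reproduce. The check has three parts: which sources exist in each arm, how many households are affected, and what follows for direction and size.

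**1. Sources by arm, as written**

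| Source | ITWL arm | Control arm |
|---|---|---|
| Visit 6–10 days after installation, core and buffer | yes | none stated |
| Monthly cohort visit and facility card | yes | yes |
| Passive chain, core and buffer | yes | yes (no limit to one arm stated) |
| Installer examinations and installer passive chain | yes | no installers |

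The control entry in the first row depends on what installation means. The article consistently installs ITWL and distributes nets. The Randomization and blinding section names the two separately: implementation, "for both ITWL installation and LLIN distribution, will be monitored closely for quality". Control households therefore have no date from which 6 to 10 days could run. The section on implementation pairs each intervention cluster with a control cluster, but only for the timing of cohort recruitment.

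**2. Households affected**

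Inputs:
- 22 clusters per arm (Sample size rationale).
- At least 275 households per cluster, of which at least 124 are in the core (Study area and participant recruitment).
- About 70 cohort households per core (Social acceptability and economic evaluations).

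Results per arm:
- Households receiving the extra visit: 22 × 275 = 6,050 in the ITWL arm; 0 stated in control.
- Cohort households with monthly active questioning: 22 × 70 = 1,540.
- Non-cohort households: 6,050 − 1,540 = 4,510, and 4,510 / 6,050 = 75 %.
- Of these, non-cohort core households: 22 × (124 − 70) = 1,188. Buffer households: 22 × (275 − 124) = 3,322.

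The recruitment section instead assumes about one eligible child per household. On that figure, 110 children would mean 110 cohort households per core, and the non-cohort share would be (275 − 110) / 275 = 60 %. The conclusion is the same.

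Non-cohort households thus have one active contact in the ITWL arm and none in control.

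**3. Direction and size**

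The sources in the ITWL arm are those of the control arm plus one. With equal true risk and equal reporting through the shared sources, the ITWL arm cannot detect fewer events. It detects more whenever the visit finds something the others would miss.

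The size needs detection probabilities that the document does not give. For illustration only, let *a* be the probability of detecting an early event at the post-installation visit, *m* at a monthly visit and *b* passively. With no true effect, and setting aside what the shared sources add in the ITWL arm:

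apparent risk ratio = *a* / [(70*m* + 205*b*) / 275]

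- *a* = 0.8, *m* = 0.8, *b* = 0.5: 0.8 / [(56 + 102.5) / 275] = 0.8 / 0.576 = 1.39.
- *a* = 0.9, *m* = 0.5, *b* = 0.1: 0.9 / [(35 + 20.5) / 275] = 0.9 / 0.202 = 4.46.

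The spread from about 1.4 to 4.5 comes entirely from the assumed inputs. It shows that the size is unknown and is not an estimate for this trial.

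**Timing.** Installation starts in late August 2015, the 12-month monitoring period starts in December 2015, and active monthly questioning is described for the study year. Some of the early window may therefore have no active source in control even for cohort households. This is an inference from dates, and the conclusion does not rely on it.

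**The case against.** The strongest reply is that the article never says it will pool events from the post-installation visit with the rest and compare totals between arms. The Data analysis section describes no adverse-event analysis, and a condensed article may leave the choice of sources to a fuller document. Comparable sources already exist, so a sensible analyst would use them. This explains why the fix is cheap, but it does not remove the fault. The article states a comparison rule, applies it to all adverse events and does not confine it to shared sources. Followed as written, the rule is biased.

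A second reply is that all core and buffer households could include control clusters, which also have cores and buffers. The missing installation date and the reference to the ITWL intervention period make this the weaker reading. If it was the intention, a sentence describing the control visit would settle the matter.

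Third, the visit is reasonable surveillance of a new household product, and over-detection errs on the cautious side. That stands. The objection is to the comparison, not to the visit, which is a single contact per household.

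Three stronger readings are tempting and are not supported:

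- **A count of spurious events.** If 2 % to 10 % of visited households reported a background complaint, that would be 0.02 × 6,050 = 121 to 0.10 × 6,050 = 605. The document gives no such rate, and the sum ignores overlap with the monthly and passive sources.
- **A wrongly stopped trial.** Discontinuation rests on a determination of potential harm by the DSMB's independent experts. No adverse-event rate threshold is stated, and the experts would know which arm had installations.
- **An invalid safety comparison throughout.** A comparison confined to the monthly cohort visits has the same ascertainment schedule in both arms, although it is unblinded.

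**Conclusion.** The point holds in a limited form. The article grades all adverse events for relatedness against the control arm, while one active source, as written, covers at least 6,050 ITWL-arm households and no control households. Installer events have no comparator at all. Early events, chiefly in non-cohort and buffer households, would be over-ascertained in the ITWL arm.

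This rests on the reading that installation means ITWL installation and that no matched control visit exists. The household counts use the protocol's minimum figures and its own estimate of 70 cohort households per core. The direction follows from the list of sources; the size cannot be obtained from the document. The primary malaria endpoint is untouched, and adverse-event rates are not a listed endpoint. The correction is still worth making because it concerns the stated basis for attributing harm and is almost free.

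**What to change.** Keep the post-installation visit and add a limiting statement to the safety section, for example: *Between-arm comparisons of adverse events, and any judgement of relatedness resting on them, use only events recorded through sources common to both arms (monthly cohort visits, health-facility cards and passive reports), shown by calendar period. Events found at the post-installation visit and events in installers are reported separately, as descriptive data for the ITWL arm only.* The DSMB tables should follow the same split. Calendar period matters because installation is rolled out cluster by cluster.

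If control households were meant to receive a visit at a matched time, state that visit and its timing instead; the household events can then be compared directly. Installer events would still need separate reporting.

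The cost is a short addition to the text and one extra table, with no added visits. The small downside is that the early post-installation events lose a randomized comparator. The change also leaves unblinded reporting in the shared sources as it is.
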